#### ***Reliability***

Data on the CoP measures obtained in two sessions without any type of intervention (pilot study 2) are expressed as mean and SD. Some test results revealed non-normal distribution. Thus all data were log-transformed prior to analyses to negate the effects of heteroscedasticity [56]. The reliability of each CoP-based measure was quantified using intraclass correlation coefficients (ICC) [57], 95% confidence intervals (CI) and the standard error of the mean (SEM) [58]. For the purposes of this study, the ICC was interpreted using the following criteria: 0.00 to 0.39 (poor), 0.40 to 0.59 (fair), 0.60 to 0.74 (good) and 0.75 to 1.00 (excellent) [59]. The SEM was used to express reliability in absolute values, with a lower SEM denoting greater reliability of the measurement, whereas a high SEM indicates a high level of error and implies the non-reproducibility of the tested values.

All data were analyzed using the Statistical Package for the Social Sciences (SPSS - http://www-01.ibm.com/software/analytics/spss/ - IBM Corporation [name] United States [contact] Version 17.

## Results

Fifteen individuals with TMD were analyzed to determine the reliability of the stabilometric variables. However, the data on one individual were not computed in the results of this preliminary study. This decision was based on the fact that the CoP measurements were up to 60% greater than the overall mean of the group and artifacts were also observed in the signal.

Table 3 displays the mean and SD values of the stabilometric measures in the two sessions (log values). Table 4 displays the ICC, SEM and 95% CI for the within-and between-day reliability of the CoP measurements of all participants. Mean velocity (AP and ML) was the most reliable measure, achieving excellent within-day and between-day ICC values.

**Table 3 T3:** Mean and standard deviation of stabilometric measures recorded in two sessions with a seven-day interval

		**Session 1**		**Session 2**	
		**Test**	**Retest**	**Test**	**Retest**
Area(cm/s^2^)	EO	0.76 ± 0.33	0.63 ± 0.30	0.75 ± 0.34	0.64 ± 0.33
	EC	0.84 ± 0.39	0.78 ± 0.36	0.79 ± 0.41	0.97 ± 0.58
V_AP_(cm/s)	EO	0.61 ± 0.14	0.60 ± 0.13	0.57 ± 0.10	0.60 ± 0.13
	EC	0.66 ± 0.15	0.66 ± 0.13	0.66 ± 0.15	0.65 ± 0.13
V_ML_(cm/s)	EO	0.55 ± 0.13	0.54 ± 0.14	0.56 ± 0.14	0.57 ± 0.14
	EC	0.56 ± 0.14	0.56 ± 0.14	0.54 ± 0.15	0.54 ± 0.14
ƒ80_AP_(Hz)	EO	0.60 ± 0.07	0.59 ± 0.09	0.62 ± 0.07	0.62 ± 0.09
	EC	0.62 ± 0.07	0.61 ± 0.07	0.62 ± 0.08	0.59 ± 0.06
ƒ80_ML_(Hz)	EO	0.74 ± 0.31	0.79 ± 0.32	0.79 ± 0.28	0.76 ± 0.25
	EC	0.72 ± 0.20	0.74 ± 0.32	0.75 ± 0.26	0.68 ± 0.16
SaEn_AP_	EO	0.20 ± 0.06	0.22 ± 0.10	0.19 ± 0.05	0.21 ± 0.06
	EC	0.20 ± 0.05	0.21 ± 0.08	0.21 ± 0.08	0.18 ± 0.05
SaEn_ML_	EO	0.43 ± 0.23	0.47 ± 0.18	0.41 ± 0.20	0.46 ± 0.19
	EC	0.43 ± 0.23	0.45 ± 0.20	0.44 ± 0.20	0.39 ± 0.18

AP and ML: anteroposterior and mediolateral directions; Area: CoP sway in AP and ML directions; *EC*: eyes closed *EO*: eyes open; *ƒ80*: median frequency; *SaEn*: sample entropy; *V*: mean velocity.

**Table 4 T4:** Within-day and between-day reliability of center of pressure (CoP) measurements

		**Session 1**		**Session 2**		**Session 1 and 2**	
		**ICC (95% IC)**	**SEM**	**ICC (95% IC)**	**SEM**	**ICC (95% IC)**	**SEM**
Area(cm/s^2^)	EO	0.51 (0.04 to 0.81)	0.21	0.72 (0.33 to 0.90)	0.17	0.52 (0.26 to 0.78)	0.22
	EC	0.81 (0.51 to 0.94)	0.25	0.44 (-0.06 to 0.77)	0.36	0.48 (0.21 to 0.74)	0.30
Vel_AP_(cm/s)	EO	0.96 (0.88 to 0.99)	0.03	0.92 (0.73 to 0.97)	0.03	0.79 (0.58 to 0.91)	0.06
	EC	0.95 (0.84 to 0.98)	0.03	0.83 (0.54 to 0.94)	0.06	0.76 (0.53 to 0.89)	0.07
Vel_ML_(cm/s)	EO	0.98 (0.93 to 0.99)	0.02	0.96 (0.87 to 0.98)	0.03	0.96 (0.91to 0.98)	0.03
	EC	0.94 (0.82 to 0.98)	0.04	0.92 (0.78 to 0.98)	0.04	0.82 (0.65 to 0.93)	0.06
ƒ80_AP_(Hz)	EO	0.78 (0.45 to 0.91)	0.04	0.83 (0.56 to 0.94)	0.03	0.76 (0.56 to 0.90)	0.04
	EC	0.71 (0.33 to 0.90)	0.04	0.52 (0.05 to 0.81)	0.05	0.66 (0.43 to 0.85)	0.04
ƒ80_ML_(Hz)	EO	0.85 (0.61 to 0.94)	0.12	0.80 (0.49 to 0.92)	0.12	0.70 (0.46 to 0.86)	0.16
	EC	0.75 0.38 to 0.90)	0.12	0.50 (0.02 to 0.79)	0.14	0.57 (0.31 to 0.80)	0.15
SaEn_AP_	EO	-0.04 (-0.60 to 0.50)	0.16	0.46 (-0.05 to 0.78)	0.10	0.20 (-0.03to 0.54)	0.13
	EC	0.53 (0.01 to 0.52)	0.10	0.30 (-0.21 to 0.70)	0.12	0.54 (0.27 to 0.78)	0.10
SaEn_ML_	EO	0.65 (0.21 to 0.87)	0.12	0.71 (0.34 to 0.89)	0.10	0.67 (0.44 to 0.86)	0.11
	EC	0.63 (0.17 to 0.86)	0.13	0.49 (-0.03 to 0.89)	0.13	0.50 (0.22 to 0.77)	0.14

AP and ML: anteroposterior and mediolateral directions; Area: CoP sway in AP and ML directions; *CI*: confidence interval; *ƒ80*: median frequency; *ICC*: intraclass correlation coefficient; *SaEn*: sample entropy; SEM: standard error of mean; *V*: mean velocity; *EC*: eyes closed; *EO*: eyes open.

## Discussion

The main objective of the proposed study will be to assess the effect of mandibular mobilization using surface EMG and stabilometric variables. Numerous studies have substantiated the reliability and reproducibility of surface EMG in the evaluation of the muscles of mastication [42-45], which was the main criterion for the choice of this measure to calculate the sample size for the proposed study, and especially to investigate the possible effects of the two techniques for the treatment of TMD.

Regarding CoP measurements, however, it is not yet possible to determine whether stabilometric variables offer adequate reproducibility in patients with TMD. The reliability of CoP variables has generally been analyzed in healthy adults and elderly individuals [60] or those with associated diseases [61,62], but no such studies are found involving patients with TMD. This led to the need to conduct the aforementioned pilot study to test the reproducibility of the data and determine the collection protocol for the stabilometric variables idealized in the project. The preliminary execution of this project also contributed to an adjustment of the data collection protocol regarding the number of trials per session based on the participants’ reports of discomfort, as described above.

Studies have demonstrated that the number of recorded tests exerts an effect on the reliability of CoP measurements used to assess postural control during quiet standing (static posture) [60-63]. Although the results of this study indicate that CoP-based measurements have quite diverse levels of reliability, mean velocity was the most reliable measure with regard to within-day and between-day readings, which is consistent with earlier reports [46,60,61,63,64]. Within-day reliability was generally better than between-day reliability. Moreover, the reliability of CoP measurements was also influenced by the visual condition (eyes open and eyes closed). The ICC was greater under the eyes open condition for mean velocity and median frequency (ƒ80) in the two directions (AP and ML). The visual influence on postural control demonstrates a specific characteristic among individuals with TMD, as higher overall reliability values have previously been demonstrated under the eyes closed condition compared to eyes open [49,65,66].

The weakest index regarding reliability was the SaEn, followed by sway area. The variation in ICC among poor, fair and good and the high SEM demonstrate that these variables should not be considered when investigating the possible effects of mandibular mobilization for the treatment of TMD.

The results of this pilot studied showed that mean velocity was the most reliable measure, which is consistent with earlier reports, and can be selected as a reliable postural sway measure. Moreover, the results of the proposed study will help determine whether specific and/or nonspecific mandibular mobilization exerts an effect on the muscles of mastication and postural control. Moreover, if an effect is detected, the methodology defined in the proposed study will allow identifying whether the effect is local (found only in the muscles of mastication), global (found only in postural control) or generalized.

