**Discussion:**

A large number of studies have employed surface electromyography to investigate the function/dysfunction of the muscles of mastication and associations with signs and symptoms of temporomandibular disorders. However, it has not yet been determined whether stabilometric variables offer adequate reliability in patients with this disorder. The results of the proposed study will help determine whether specific and/or nonspecific mandibular mobilization exerts an effect on the muscles of mastication and postural control. Moreover, if an effect is detected, the methodology defined in the proposed study will allow identifying whether the effect is local (found only in the muscles of mastication), global (found only in postural control) or generalized.

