#### ***Surface EMG***

Surface EMG signals from the right and left masseter and right and left anterior temporal bundle will be recorded with disposable surface electrodes (Ag/AgCl - Noraxon^®^ - http://noraxon.com - [name]. [contact]) attached to the belly of the muscle in the region with the greatest tonus after the volunteer performs moderate intercuspation (clenching of the teeth). The inter-electrode distance will be 20 mm from center to center. The sites for the electrodes will be cleaned with a cotton ball soaked in alcohol to diminish the impedance between the skin and electrodes [39]. A rectangular metallic electrode measuring 3 cm × 2 cm coated with Lectron II conductive gel (Pharmaceutical Innovations^®^ - http://www.pharminnovations.com - [name] [name]) to increase the conduction capacity and impede interference from external noise will be attached to the left wrist of the volunteers for reference.

The bipolar EMG signals will be amplified using an eight-channel module (EMG System do Brasil Ltda^®^ - http://www.emgsystem.com.br - [name]. [name])) consisting of a conditioner with a band pass filter with cut-off frequencies of 20 to 1000 Hz, an amplifier gain of 1,000 and a common mode rejection ratio > 120 dB. All data will be acquired and processed using a 16-bit analog to digital converter (EMG System do Brasil Ltda^®^ - http://www.emgsystem.com.br - [name]. [name])) at a sampling frequency of 2 kHz.

For the recording of the EMG signals, the participants will remain seated in a chair with feet apart and hands resting on the lower limbs. To standardize the EMG potentials of the four muscles analyzed with tooth contact, two strips of Parafilm M^®^ (American National Can TM, Chicago, IL, USA) will be folded into five parts (3 mm in thickness) and positioned on the first and second mandibular molars (bilateral) of each subject [40]. Four seconds of maximum voluntary clenching (MVC) will be recorded three times, with a three-minute interval between readings.

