After five minutes of rest, the recording of EMG activity will be performed three times successively under the following conditions: i) rest position: the subjects will be asked to relax and maintain the maxillary and mandibular teeth without contact; ii) maximal intercuspation (isometric): the subjects will be ask to clench the teeth as hard as possible and maintain the same level of contraction (tooth contact); and iii) chewing (isotonic): the subjects will be instructed to mildly and symmetrically bite down (chew) on the two strips of Parafilm M^®^ (positioned bilaterally) in time with a metronome adjusted to 60 beats per minute.

For the EMG signals recorded in rest position and during chewing, a two-minute interval will be allowed between readings. For maximal intercuspation, a five-minute interval between readings will be used. The data collection time will be 15 seconds for the rest position and chewing condition and 8 seconds for maximal intercuspation.

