### Signal processing

#### ***Stabilometric parameters***

Displacement from the center of pressure (CoP) in the anteroposterior (AP) and mediolateral (ML) directions will be used to analyze body sway, as in the preliminary study (pilot study 2). CoP data will be filtered with a Butterworth low-pass filter with a cut-off frequency of 10 Hz [46]. Postural sway will be quantified by means of two common scale-dependent variables: CoP sway area as an indicator for magnitude of CoP movements and CoP mean velocity and frequency as indicators of the efficiency of postural control. As an indicator for the regularity of CoP movements, a scale-independent variable denominated sample entropy (SaEn) will be used. Each parameter is briefly described below:

– Sway area (cm^2^) will be estimated by fitting an ellipse to the CoP data (AP versus ML) that encompasses 95% of the data; [48]

– Mean velocity (cm/s) of the CoP in both AP and ML directions will be calculated by taking the total distance traveled and dividing it by the time of the trial; [49]

– Frequency (Hz) of CoP displacement will be determined by the frequency at which 80% of the CoP spectral power is below. The 80% value was chosen based on the study by Baratto *et al*. (2002) [50], who suggest that this value is a better discriminator for CoP data than other spectral measurements;

– SaEn is a method for quantifying the regularity of a time series [51,52] and reflects the conditional probability that two sequences of 'm’ consecutive data points that are similar to each other will remain similar when one more consecutive point is included. Being 'similar’ means that the value of a specific measure of distance is less than 'r’. Therefore, SaEn is a function of m and r parameters [53]. The embedding dimension, m, and the tolerance distance, r, will be set to m = 3 and r = 30% of standard deviation of the data sequence [54]. To render an outcome for the scale-independent SaEn, the CoP data in both AP and ML directions will be normalized to unit variance by dividing the time-series in question by their respective standard deviation [55]. Values close to zero indicate greater regularity, while values closer to two indicate greater entropy in the signal being analyzed. In the present study, a decrease in sample entropy (that is, more regular sway fluctuations) will be interpreted as a decrease in the effectiveness of postural control.

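### The local/global/generalized label treats a non-finding in one domain as evidence of no effect there, and the design cannot support that

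*Protocol article*

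**What the plan says.** The Discussion says that, if an effect is found, the study "will allow identifying whether the effect is local (found only in the muscles of mastication), global (found only in postural control) or generalized". The Abstract repeats the promise: "if an effect is detected, the methodology defined in the proposed study will allow identifying whether the effect is local".

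The Data analysis section gives repeated-measures ANOVA or Friedman within groups, and one-way ANOVA or Kruskal-Wallis between groups, variable by variable. It describes no comparison of the EMG result with the sway result and no criterion for concluding that a domain is unaffected.

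Only EMG was used for sizing. The Discussion cites its established reliability, "which was the main criterion for the choice of this measure to calculate the sample size for the proposed study". Pilot studies gives the calculation: right temporal muscle, maximal intercuspation, a fall from 1.19 to 1.08 over five sessions of nonspecific mobilization, SD 0.14, power 0.80, 13 individuals.

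The candidate outcomes are:
- **EMG:** "Surface EMG signals from the right and left masseter and right and left anterior temporal bundle will be recorded". The Surface EMG section lists three recording conditions: rest, maximal intercuspation and chewing.
- **Sway:** Stabilometric parameters lists "CoP sway area as an indicator for magnitude of CoP movements and CoP mean velocity and frequency as indicators of the efficiency of postural control", and adds that "a scale-independent variable denominated sample entropy (SaEn) will be used". Each is recorded with eyes open and with eyes closed. The Discussion, however, says that sample entropy and sway area ought not to be used to study treatment effects, and that mean velocity can be chosen.

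**The concern.** To call an effect local, the trial must conclude that postural control did not change. To call it global, it must conclude that the masticatory muscles did not change. A non-significant test shows neither unless the study could reliably have detected an effect of interest, and no calculation in the article addresses that for sway or for any between-group comparison. The comparator makes this sharper. The Background reports that massage of these muscles lowers EMG activity, and massage is the control, so a null between-group EMG result may mean that both arms worked.

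The rule is also loose in the other direction. No outcome is named as deciding either domain, so a finding on any muscle, condition, sway variable or visual condition could be taken as the effect being present there.

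What is at stake is the article's stated interpretation of a positive result, given in both the Abstract and the Discussion. Readers could be told that mobilization acts only on the muscles, or only on posture, when the data do not show it.

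**Working it through.** **1. The plan's own figure.** Inputs from Pilot studies: difference 1.19 − 1.08 = 0.11, SD 0.14, power 0.80. Alpha is not stated; two-sided 0.05 is assumed. For a paired change, n = ((1.960 + 0.842) × 0.14 / 0.11)² = 12.7, rounded up to 13. This reproduces the stated 13, with 0.14 read as the SD of the change. The two-group formula gives 2 × 12.7 = 25.4, or 26 per arm, which does not. So 13 is a within-group size.

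**2. Between-group power.** Assume 13 per group (the article does not say whether 13 is per group or in total) and the same 0.11 and 0.14. The noncentrality is (0.11/0.14) × √(13/2) = 2.00 on 24 df, and the t-test power is 0.49. A three-group ANOVA with one group differing gives 0.50. If 13 is the total, power is about 0.15 to 0.21.

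**3. A true effect in both domains, one test per domain.** Sway has no effect size in the article, so the same power is assumed for it, with domains independent. P(generalized) = p², P(local or global) = 2p(1 − p), P(none) = (1 − p)².

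| Power p | Generalized | Local or global | None |
|---|---|---|---|
| 0.485 | 0.24 | 0.50 | 0.27 |
| 0.80 | 0.64 | 0.32 | 0.04 |

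**4. The same truth, any hit in a domain counts.** This was simulated with normal tests, every outcome carrying the effect, 12 EMG outcomes and 14, 8 or 4 sway outcomes. At 49% power per outcome, the label is wrongly local or global in 14%, 18% and 26% of trials at within-domain correlation 0.5, and in 35%, 37% and 40% at correlation 0.8. At 80% power per outcome, the ranges are about 1–4% and 8–12%.

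**5. Outcome count.** EMG: 4 muscles × 3 conditions = 12. Sway under Stabilometric parameters: area (1) + velocity AP/ML (2) + frequency AP/ML (2) + entropy AP/ML (2) = 7, × 2 visual conditions = 14. Without area and entropy: 4 × 2 = 8. Mean velocity only: 2 × 2 = 4. Totals: 26, 20 or 16.

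**6. No true effect, one between-group test per outcome at 5%.** With independent outcomes, P(some label) = 1 − 0.95^k. The correlated columns are simulated with normal tests.

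| k | Independent | Correlation 0.5 | Correlation 0.8 |
|---|---|---|---|
| 26 | 0.74 | about 0.56 | about 0.35 |
| 20 | 0.64 | about 0.49 | about 0.31 |
| 16 | 0.56 | about 0.42 | about 0.28 |

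A three-group ANOVA simulation with 13 per group gave slightly higher rates: 0.59, 0.50 and 0.45 at correlation 0.5, and 0.37, 0.32 and 0.29 at 0.8.

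**7. A truly local effect read as generalized.** This needs one false sway finding: 1 − 0.95^14 = 0.51, 1 − 0.95^8 = 0.34, 1 − 0.95^4 = 0.19 (independent outcomes, hence upper figures).

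**The case against.** The strongest reply has four parts.

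- **The number of outcomes is not a firm 26.** The Discussion sets aside area and entropy just before the claim and points to mean velocity. This stands. The range is 16 to 26, and the Discussion and Stabilometric parameters must be reconciled.
- **Outcomes are correlated.** They are left and right muscles, two sway directions and two visual conditions in the same people. This stands too. A reader might infer that chance decides the label, or that an ineffective treatment would usually receive one. The 56–74% figures behind that need independence; at correlation 0.8 the rate is 28–35%.
- **The two error rates use different rules.** The 50% and 32% mislabelling figures assume one test per domain, while the false-label rates assume that any hit counts. This is correct, so they should not be read as holding together. Under the any-hit rule at 49% power per outcome, mislabelling is about 14–40%, and it is small at 80% power with correlation 0.5.
- **Alpha, adjustment and the decision rule may be in an analysis plan not shown.** A reader might infer that the tests are unadjusted. The article does not say so, and its silence is not the finding.

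It is also fair that the sentence is conditional on an effect being detected, and that the stated main objective is to assess the effect of mobilization.

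None of this rescues the label. An alpha adjustment elsewhere would not turn a non-finding into evidence of no effect.

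**Conclusion.** The point holds as a fault in a stated rule of inference. The local and global labels require evidence of absence that separate per-variable tests do not supply, in a trial sized on one within-group EMG change.

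The size depends on assumptions. With 13 per group, two-sided 5%, the pilot EMG effect and equal power assumed for sway, a true effect in both domains is mislabelled about 50% of the time with one test per domain (32% at 80% power). If any hit counts, at 49% power per outcome and correlation 0.5 to 0.8, it is about 14–40%. With no effect, and each of 16 to 26 outcomes tested once at 5%, a label appears about 28–56% of the time at those correlations. Additional within-group tests or evaluations, if they also counted, would raise this.

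The 49% is not a stated property of the trial: it rests on reading 13 as per group, and its use for sway is purely illustrative.

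**What to change.** 1. Delete the exclusivity wording from the Abstract and the Discussion.
2. Rest the claim on one named outcome per domain. For EMG, use the normalized right temporal RMS in maximal intercuspation, which is the sizing variable. For sway, use one mean velocity measure. Mean velocity is four outcomes (AP/ML by eyes open/closed), so one must be chosen in advance. Mediolateral with eyes open, for example, has the highest between-day ICC in Table 4 (0.96).
3. Name the group contrast and test both outcomes at Evaluation 3 with Holm over the two. Treat all other outcomes as exploratory.
4. Report the between-group difference and 95% confidence interval in both domains. Where an interval is inconclusive, draw no conclusion for that domain instead of calling the effect local or global.
5. Reconcile Stabilometric parameters with the Discussion on whether area and sample entropy are analysed.

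The trial is already recruiting, so this should be settled before the statistician is unblinded.

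**Cost.** The conclusion becomes more modest, and power per domain falls at the first Holm step. With 13 per group and the pilot effect, the t-test at 0.025 has power of about 0.37, against 0.49 at 0.05. To keep 80% power at 0.025 on the same inputs would take 2 × ((2.241 + 0.842) × 0.14 / 0.11)² = 30.8, or 31 per arm, against 26 at 0.05.

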## Trial status

This trial is currently recruiting patients.

## Abbreviations

Ag/AgCl: Silver/silver chloride; ANOVA: Analysis of variance; AP: Anteroposterior; CG: Control group; CI: Confidence interval; CoP: Center of pressure; COPAP: Anteroposterior center of pressure; COPML: Mediolateral center of pressure; EC: Eyes closed; EMG: Electromyography; EO: Eyes open; f80: Median frequency; ICC: Interclass correlation coefficient; ML: Mediolateral; MVC: Maximum voluntary contraction; NMG: Nonspecific mobilization group; RDC/TMD: Research Diagnostic Criteria for Temporomandibular Disorders; RMS: Root mean square; ROM: Range of movement; SaEn: Sample entropy; SD: Standard deviation; SEM: Standard error of mean; EMG: Electromyography; SPSS: Satistical package for social sciences; TMD: Temporomandibular disorder; TMJ: Temporomandibular joint.
